### WP1: The epidemiology of severe mental illness, compulsory hospitalisation, and outpatient commitment

3.1

This WP will answer three categories of epidemiological questions concerning people in contact with specialist mental health or addiction services in Norway in 2015–2016.

The first category will compare short and long‐term trajectories of persons with and without SMI in voluntary and compulsory care. Additionally, the outcomes of these persons will be compared to a control group from the general population.

The second category will describe the extent of geographical variation inPrevalence of SMI.All mental health service use for people with SMI, including referrals to specialist mental health care and per‐person use of antipsychotic medication.Compulsory inpatient and outpatient health service use.

We will test the competing hypotheses that providers who are less likely to use one form of compulsion may be more likely to use the other, or that providers who use little inpatient compulsion also tend to use little OC.

Data will be aggregated to geographical regions, specifically catchment areas to community mental health centres, based on residency. The variation will be described as population‐based rates and as the proportion of inpatients and outpatients with a compulsory referral or legal status. The relationship between urbanicity and risk of psychosis (Fett et al., 2019) has not previously been documented in Norway, but will also be covered in WP1.

The third category will explore associations between rates of compulsory care per population and indicators of social inequality and socio‐economic position in the catchment areas, such as the proportion of high school dropouts; median income in the area; and unemployment rate.

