### WP2: Short and long‐term causal effects of compulsory inpatient and outpatient mental health care, including administration of medication without consent

3.2

The main objective of WP2 is to estimate the causal effect of compulsory mental health care on health and social functioning outcomes for people with SMI, potentially including long term costs to the public purse and society associated with these differences. We will use variation in clinical practice among catchment areas as IV to estimate the causal effect of compulsory care on multiple outcomes (see Figure 5). The primary analyses will be restricted to (a) people with SMI; and (b) people who are referred to compulsory inpatient mental health care.

We expect that patients on the margin of compulsory care after discharge will be treated differently depending on whether they live in areas with higher or lower tendency to use OC. Since OC is most often used to ensure medication compliance (Riley et al., 2019) and almost all people on OC receive antipsychotic treatment (Barkhuizen et al., 2020; Riley et al., 2019; Rugkåsa et al., 2015), we will use provider preference for use of OC as a proxy to measure the effect of administration of medication without consent. This WP will also test assumptions that must be fulfiled for IV‐estimates to credibly reflect causal relationships (Widding‐Havneraas et al., 2021).

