### Assumptions of provider‐preference instrumental variables

5.2

First, the *relevance criterion* implies that the instrument must be correlated with the treatment variable. We intend to generate IVs at the regional provider level of catchment area to Community Mental Health Centres (Ruud and Friis, 2021). Stable geographical variations in compulsory hospitalisation between catchment areas have been documented, and more than 80% of variation in ranked rates of compulsory hospitalisation per population could be predicted by the area rankings for the previous year, while 50%–75% of variation in inpatient rates could be predicted this way (Hofstad et al., 2021), suggesting that provider preference for compulsory care can be a strong instrument (Hernán and Robins, 2020).

Second, the *exclusion restriction assumption* implies the instrument should only impact the outcome through treatment. This means that service providers' preferences for using compulsory mental health care in an area should impact whether involuntary care is initiated, while being uncorrelated with outcomes through other paths. We will use a *negative control population* to test this assumption (Lipsitch et al., 2010); since provider preference should have no impact on those who were not in contact with mental health services, the impact of the instrument on the outcome should be zero in the control cohort.

Theoretically, the instrument will control for unobserved and observed characteristics of individuals that can affect the outcome. However, instrument‐outcome confounders can still bias estimates, in which case the instrument would not be equivalent to “as‐good‐as‐random assignment” (Garabedian et al., 2014). So the third *assumption of no confounding* requires that there are no unmeasured common causes of the instrument and the outcome. This will be tested indirectly through balance tests of baseline covariates (Brookhart and Schneeweiss, 2007).

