The fourth assumption of *monotonicity* ensures that the estimand can be interpreted as the Local Average Treatment Effect (LATE). Individuals who clearly fill criteria for compulsory care are assumed to be subject to compulsion in all areas, while persons where compulsory hospitalisation is clearly not indicated are not subject to compulsion anywhere. Consequently, the estimand represents the effect of compulsory care for people with SMI at the margin/in the grey zone of compulsory care; individuals who are expected to be treated differently if they live in areas with a high versus a low use of compulsory care (See Figure 2). By design, we know that all people who are assigned to the treatment (compulsory care), will receive it, thereby ensuring no ‘*defiers’*.

Subject‐matter knowledge, required for all but the first assumption, will be provided by project group members, as well as service‐users and providers. Topics meriting investigation include whether the variation is random or remains stable over time. Are there differences in case mix, with different prevalence of SMI between areas? Is there risk of selection bias, where service users residing in low‐compulsion areas, but require compulsory hospitalisation, are transferred to areas that use more compulsion?

In general, people are unaware whether rates of compulsory mental health care in their catchment area are high or low compared to the country average. Given the retrospective baseline, the quasi‐experimental framework is similar to a double‐blinded experiment where neither service users nor providers could identify the treatment. While some clinicians may have recognised that the use of compulsory care tended to be higher or lower within their area, they were unaware that they partook in a natural experiment. There is also little reason to expect that people self‐selected to areas based on compulsory hospitalisation rates, thereby reducing the risk of selection bias.

Even if the exclusion restriction assumption is violated, the ‘*reduced form’* can provide an unbiased estimate of the effect of the instrument on the outcome (Chernozhukov and Hansen, 2008), and will answer whether a higher or lower propensity for compulsory care results in superior, worse or similar outcomes for patients.

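### Section 5.2 says defiers are excluded by design because ordered compulsory care is always received; this concerns the treatment, not the area-preference instrument, and gives monotonicity no support

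*Protocol article*

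**What the plan says.** The instrument is defined by area. Section 3.2 (WP2) states: "We will use variation in clinical practice among catchment areas as IV to estimate the causal effect of compulsory care on multiple outcomes". Section 5.2 fixes the level: "We intend to generate IVs at the regional provider level of catchment area to Community Mental Health Centres".

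Section 5.2 then makes monotonicity the condition under which the IV estimand is a local average treatment effect (LATE). It offers two supports.

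- Clear-cut cases: "Individuals who clearly fill criteria for compulsory care are assumed to be subject to compulsion in all areas", with a matching statement that clearly non-indicated cases are compelled nowhere. The estimate then concerns the people in between, described as "individuals who are expected to be treated differently if they live in areas with a high versus a low use of compulsory care".
- A closing claim: "By design, we know that all people who are assigned to the treatment (compulsory care), will receive it", from which the section concludes that there are no defiers.

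The following paragraph of section 5.2 says that subject-matter knowledge is needed for every assumption except relevance. Section 3.1 (WP1) sets out two competing hypotheses about the forms of compulsion. One is that "providers who are less likely to use one form of compulsion may be more likely to use the other"; the other is that low use of one goes with low use of the other.

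**The concern.** The closing claim uses the word assigned for the treatment, whereas in an IV analysis the thing assigned is the instrument. Monotonicity requires that anyone who would be compelled in a lower-preference area would also be compelled in every higher-preference area. Whether a compulsory decision, once made, is carried out has no bearing on that.

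The LATE reading for grey-zone patients is the central causal claim of WP2. If some patients respond to area preference in the opposite direction, and compulsion affects them differently, the IV estimate can be larger than any true effect, vanish, or take the wrong sign. Section 6 expects the results to bear on policy and legislation, so the size and sign of a grey-zone effect matter. A reader told that defiers are excluded by design would see no reason to look for them.

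**Working it through.** **Step 1: the definition against the text.** Take two areas, low-use and high-use, and write D(low) and D(high) for whether a given person would receive compulsory care in each. A defier has D(low) = 1 and D(high) = 0. The protocol's sentence says that whoever is given a compulsory decision receives compulsory care. That holds for a defier too: in the low-use area the decision is made and carried out, and in the high-use area no decision is made. Full receipt is therefore compatible with any share of defiers. A simulation of 4 million persons with assumed shares (20% always compelled, 60% never, 15% compliers, 5% defiers) and every decision carried out shows 100% receipt alongside 5.0% defiers.

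**Step 2: what the clear-case assumption covers.** It fixes D(low) = D(high) at the two extremes. Those people contribute nothing to the first stage. For the grey zone the text says only that care differs by area, not that it differs in the same direction for everyone.

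**Step 3: whether the direction could differ.** Section 4.4 describes a treatment criterion and a danger criterion, with the capacity requirement applying only where danger is not involved. Section 2.5 lists bed capacity, assessment of decision-making capacity and interpretation of legal criteria as separate possible sources of area variation. Two areas could therefore rank one way for one type of patient and the other way for another. If inpatient compulsion and outpatient commitment (OC) are pooled as one treatment, the substitution hypothesis of section 3.1 could, if true, be a further route.

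**Step 4: consequence.** The protocol gives no shares or effects, so there is no figure of its own to reproduce; all values below are assumptions. With complier share p_c and effect d_c, and defier share p_d and effect d_d:

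- first stage = p_c − p_d
- reduced form = p_c·d_c − p_d·d_d
- IV estimate = (p_c·d_c − p_d·d_d)/(p_c − p_d)
- mean effect among all whose care depends on the area = (p_c·d_c + p_d·d_d)/(p_c + p_d)

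Effects are in percentage points (pp).

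| p_c | p_d | d_c | d_d | First stage | Reduced form | IV estimate | Mean effect |
|---|---|---|---|---|---|---|---|
| 15% | 0% | −2 | n/a | 15% | −0.30 | −2.0 | −2.0 |
| 15% | 5% | −2 | −2 | 10% | −0.20 | −2.0 | −2.0 |
| 15% | 5% | −2 | +2 | 10% | −0.40 | −4.0 | −1.0 |
| 12% | 8% | −2 | +2 | 4% | −0.40 | −10.0 | −0.4 |
| 15% | 5% | −5 | −15 | 10% | 0.00 | 0.0 | −7.5 |
| 15% | 10% | −5 | −15 | 5% | +0.75 | +15.0 | −9.0 |

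Third row: (0.15 × −2 − 0.05 × 2)/0.10 = −0.40/0.10 = −4.0, against (0.15 × −2 + 0.05 × 2)/0.20 = −1.0. Last row: (0.15 × −5 − 0.10 × −15)/0.05 = 0.75/0.05 = +15.0, although the effect is negative in both groups. The simulation in step 1, run with effects of −10 and +10 pp, gave −19.5 pp where the formula gives −20 pp.

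**Step 5: the other assumptions.** Section 5.2 cites year-to-year stability of area rankings for relevance, a negative control population for the exclusion restriction, and balance tests for no confounding. It names nothing specific for monotonicity. Section 3.2 promises in general terms that the IV assumptions will be tested.

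**The case against.** The strongest reply is that the by-design sentence is not the only support. If all areas order patients on one common scale of severity and risk, and differ only in where they set the cut-off, monotonicity follows. The grey-zone account in sections 2.4 and 5.2 suggests that picture. The call for subject-matter knowledge shows that the matter is not treated as closed, and section 3.2 commits WP2 to testing the IV assumptions. All of this stands. A reader might infer that the LATE interpretation has no support at all, or that monotonicity is false here; the document supports neither. But the single-scale picture is an assumption, and it is not what the by-design sentence argues.

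A second reply is that a condensed article may leave the choice of first-stage checks to a fuller plan. That also stands: the absence of a listed check is not the error. The error is a stated reason that is invalid.

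Third, the section 3.1 hypothesis is one of two competing ones, and an area-level trade-off between forms of compulsion does not by itself make any individual a defier. Section 3.2 already uses OC preference separately for patients after discharge, and section 5.1 says separate analyses of compulsory observation and compulsory care may be relevant. So pooling could create defiers; it cannot be said that it would.

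Fourth, equal effects in compliers and defiers leave the estimate unchanged, and the reduced form needs no monotonicity. Both are correct and limit the reach of the point.

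**Conclusion.** The by-design sentence is wrong as written and should not stand as a reason for excluding defiers. Monotonicity relative to area preference remains an untested assumption, made plausible at the extremes but not fixed in direction within the grey zone.

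The size of the problem cannot be derived from the document. Under assumed shares and effects it runs from no distortion (no defiers, or equal effects), through −4 pp where the complier effect is −2 pp and the mean among those affected is −1 pp, to a reversal of sign. These figures use a two-area simplification and show what is possible, not what is expected.

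A reader might conclude that WP2 as a whole fails. It does not. The flaw touches the LATE and grey-zone wording. The reduced form remains interpretable as the effect of area propensity, which is also how the three scenarios in section 6 are worded, although it is not then an average effect of compulsion on individuals.

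**What to change.** 1. Delete the by-design sentence. State monotonicity as an assumption: a person who would be compelled in an area of lower preference would also be compelled in any area of higher preference.
2. Check that the first stage is non-negative in pre-set strata such as diagnosis group, sex and age. Repeat the check with the instrument built from the complementary strata.
3. Keep inpatient compulsion, compulsory observation and OC as separate treatments, each with its own instrument.
4. Where a stratum reverses, use stratum-specific instruments, or drop the grey-zone LATE wording and rely on the reduced form.
5. Say that these checks can reveal violations but cannot exclude them, since defiers may be hidden within a stratum whose first stage is positive overall.

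The cost is one rewritten sentence and a few first-stage regressions. Table A1 already lists diagnosis, gender, age, involuntary admission and OC. The downside is that some estimates may lose the simple LATE label.

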### Ethical approval and consent

5.3

This project was approved by the Regional Ethical Committee for Medical and Health Services Research, Norway: REC South‐East, Committee D (REC number 2017/2436/REC south‐east D). The committee considered that the project had potential for considerable social utility, while preserving the participants' welfare and integrity. Furthermore, informed consent was considered infeasible to obtain, and criteria for exemption from the duty of confidentiality were fulfiled. Based on the projects' objectives and potential usefulness of results, the Committee approved that information from the different registries could be combined. A Data Protection Impact Assessment was performed and updated during the project development.

## DISCUSSION

6

This protocol describes a novel approach to informing the debate about the effectiveness of compulsory mental health care, which can produce important new knowledge of societal interest and importance.

We envision three possible scenarios for each outcome, with different consequences for the ongoing debate; policy and legislation; and evidence‐based medicine. One scenario, which is not unlikely, is that we find no difference in long term outcomes for patients in areas with a higher or lower propensity for compulsory care usage. In this case, the burden of proof of effectiveness rests on the areas that frequently use compulsory care, given the many ethical challenges inherent in the practice.

A second scenario is that we find more positive long‐term outcomes in areas with more compulsory care. This scenario might put empirical data at odds with the ethical position that compulsion can rarely, if ever be justified, and can support compulsion use in some contexts. However, it will not invalidate many of the strong arguments for limiting compulsion, such as the inherent risk of harm and lack of respect for self‐determination.

The third scenario is more negative outcomes in areas with a higher propensity for using compulsion. This can indicate that benefits from compulsion are limited, with problematic secondary effects that harm services user/provider relations and impede compliance. Such a finding would provide more clear implications and strongly support continued efforts at reducing compulsion.

The observed geographical variation in compulsory mental health care in Norway reflects international trends. The findings from this project might also help inform the debate in countries that lack access to high‐quality registry data at a population level.

The extent to which the research community is detached from the controversy is questionable. While some variation in viewpoints exist, it appears the research community leans towards reducing coercion, as reflected in names such as FOSTREN: Fostering and Strengthening Approaches to Reducing Coercion in European Mental Health Services and ReCoN: Reducing Coercion in Norway. Our project group acknowledges the ethical challenges inherent in coercive mental health care (Chieze et al., 2021), but remains open to arguments from both sides of the controversy. Our group consists of individuals with differing opinions, ranging from those who believe compulsory care is rarely justified to those who believe it is often necessary. We aim to maintain a neutral position and prioritise empirical evidence in determining the best approach for patients. We are committed to publishing all findings, including null or unexpected results.

## ETHICS STATEMENT

Current ethics approvals last from 2022 to 2030. The project may be extended granted ethics approval and additional funding.

## Data Availability

Approvals from ethical committees and registry owners are limited to this project. Regulations and ethics approvals prohibit that the data be made public.

## Appendix

**TABLE A1 mpr1980-tbl-0001:** Data sources for the project, with examples of available variables.

National register name	Variables
Norwegian patient register (NPR)	ICD‐10 diagnosis code (F‐diagnoses); institution; in/out date; referral status; judicial reason for stay; involuntary admission;Outpatient commitment; profession deciding legal status
The central population register (CPR)	Gender; age; in/out migration; categories of immigration background; current municipality
The central penal and police register (SSP)	Charges for nine crime groups: 1. Property theft; 2. Other offences for profit; 3. Criminal damage; 4. Violence and maltreatment; 5. Sexual offences; 6. Drug and alcohol offences; 7. Public order and integrity violations; 8. Traffic offences; 9. Other offences); date of crime; prison; victim of crime
Norwegian cause of death registry	Cause of death; month
Norwegian education database (NUDB)	Highest completed level of education; mother's/father's educational level;Ended high school education before completion (“dropout”)
Tax, income and welfare registry	Income; work assessment allowance; social assistance; disability pension; unemployment
Norwegian prescription database (NorPD)	Medications for psychiatric disorder (chapter N in the ATC system); defined 24 hours dose (DDD); prescription date (quarter)
Municipal patient and user register (KPR)	Type of service; type of function; private help; type of residence; extent of service (hours pr. week);Refused service; municipality
Control and health reimbursement register (KUHR)	Types of injuries/problems (somatic and psychiatric); for treatment in first line emergency clinics
Municipal data from statistics Norway	Proportion of high school dropouts; median income; bed capacity in mental health care
Municipal data from Norwegian labour and welfare administration	Unemployment rate
